### The evaluation of feasibility and performance

The evaluation of feasibility is based on the knowledge of how parents have taken part in the study and how they have completed the questionnaires of ePIPARI at different age points. Furthermore, the anonymous survey of user-experience provides descriptive information on how parents have experienced the questionnaire, the technical usability of the ePIPARI, and its content.

The validity of the ePIPARI is evaluated based on its ability to identify children and parents in need of further support and clinical interventions in comparison to clinical visits. The outcomes to be compared are: concerns requiring clinical intervention including specialist consultations, further investigations, additional controls/follow-up visits, prescription medication or supplements or referral for treatment or therapy.

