## Methods

### Aims

The aim of this prospective study is to investigate whether the ePIPARI is a feasible and valid tool for follow-up of preterm infants in identifying children and families in need of further clinical interventions or support compared to clinical follow-up. We hypothesize that 1) ePIPARI is a feasible tool for the follow-up of preterm infants and their parents, and 2) it is comparable to routine clinical follow-up in recognizing children and parents in need for requiring interventions.

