#### Measures of the web-based follow-up

##### Health and growth

At every age-point there are general questions of health, growth, nutrition (type of milk, dietary supplements, solid food, vitamins), eating difficulties and medications, bowel function, skincare, vision and hearing and sleeping. Growth is evaluated by requesting the growth measures (weight, length, head circumference) from the last visit to the public well-baby clinic. Growth is evaluated using the Finnish age and sex specific growth charts and the growth screening program. General health/illness is evaluated by questions on any possible underlying illnesses, acute and previous infections, and different symptoms, for example, difficulties in breathing, posseting, constipation, and crying. Clinical problems are evaluated with categories of concern. Information on the sleeping habits of the child is also asked at each age point. A Patient and Public Involvement approach is included by asking the parents questions about concerns related to their child and opinions on the survey; “What would you like us to ask?” and “Did you find these questions relevant?”.

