### Participants and recruitment procedure

The recruitment process is ongoing. Parents of all preterm children, who meet the inclusion criteria during 4/2019–12/2022 are approached before discharge and asked to participate in the “ePIPARI—web-based follow-up of preterm infants”. The inclusion criteria for the infants and the parents are 1) infant is born before 34 gestational weeks, 2) infants have systematic developmental follow-up in pediatric unit in Turku University Hospital and 3) parents speak Finnish, Swedish or English. Inclusion criteria for participating only in the two-year corrected age was that the child is born before 32 gestational weeks during 2019–2021. We excluded infants, who didn’t have clinical follow-up in Turku University Hospital and parents, who couldn`t speak Finnish, Swedish or English.

Recruitment takes place in the neonatal intensive care unit by a registered nurse or a PhD-student ([name]) and the link for registration is sent to the parents’ email. After registration, parents log into ePIPARI via email or via a Mobile App by using a secure strong recognition. Advice and support for logging in is provided by a nurse before discharge. All preterm born children have the routine follow-ups regardless of their participation in the study.

The ongoing data collecting process is as follows: A digital invitation to complete the age-point specific questionnaires is sent two weeks prior to each age-point to parents’ email or to Mobile App. Parents can complete the questionnaires together or only by another, but queries related to family well-being are sent to both parents separately (Table 1). Reminders are sent if the questionnaires are not filled in. The aim is for the questionnaires to be completed before the clinical follow-up visits and so that afterwards the answers can be compared to the (written) medical records made in the clinical visits. The staff of the Pediatric unit will be blinded for the data of the ePIPARI so that it does not affect their assessment during clinical visits. Experienced medical doctors evaluate the answers of the questionnaires at two weeks intervals and estimate the amount of concern based on the responses and pre-set cut-off points. If there is significant concern that was not evident during the clinical follow-up visit, the medical doctor contacts the family or staff of the neonatal follow-up clinic.

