### Plan for statistical analysis

Data will be presented using descriptive statistics: mean values (SD) for normally distributed data, median (range/min, max) for data that are not normally distributed, and counts with percentages for categorical data.

The main comparison between digital assessment and clinical evaluation for each timepoint will be done with McNemar test (binary categorization) or Bowker test (more than two categories) for disagreement. Digital assessment will be categorized with different thresholds or a traffic light model (“child is developing typically”, “a possible risk or a clear risk”) and clinical assessment will be categorized to categories: “no concern”, “concerns requiring clinical intervention including specialist consultations, further investigations, additional controls/follow-up visits, prescription medication or supplements or referral for treatment or therapy”. Also, agreement and it’s 95% confidence interval will be calculated. Furthermore, sensitivity, specificity, positive and negative predictive values will be calculated (compared to clinical assessment).

Pearson’s or Spearman’s correlation coefficients will be generated to evaluate the linear relation between continuous variables.

In addition, to study the association between predictor and response variables within ePipari or clinical assessment visits, linear models or logistic regression models can be built up. The effect of confounding factors (such as socio-economic status, pregnancy week when child was born) will be taken into account, as appropriate. For those measurements which are evaluate repeatable, linear mixed models suitable for repeated measurements will be used.

Statistical analyses will be performed using SPSS version 29 or later or SAS System, version 9.4 for Windows or later. Two-sided p-value < 0.05 will be considered as statistically significant. Confidence intervals of 95% will be calculated, especially for feasibility part of the study.

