## Discussion

This paper describes the study protocol of the web-based follow-up tool ePIPARI for preterm infants using routine clinical follow-up visits in Turku University Hospital, Finland, as comparison. Evidence based and cost-efficient follow-up systems for preterm infants are needed to improve early identification of problems related to prematurity, to enable timely intervention and support for preterm infants and families, to monitor the quality of neonatal care and follow-up, and harmonize practices. Our systematic and intensive evidence-based follow-up enables the development of such a follow-up protocol.

The purpose of this ePIPARI-project is to create more individualized follow-up through web-based monitoring for very preterm infants; reduce the number of routine visits for those who grow and develop well without compromising their safety, and on the other hand provide targeted, time-specified, and more intensive care and support for those in need. ePIPARI could also enable follow-up and support for late-preterm infants for whom systematic follow-up in special health care services cannot be generally provided due to limited staff resources. We expect that digital monitoring will provide additional benefits to families; ePIPARI is a channel for dissemination information and support and may support a flexible follow-up tailored to the needs of the family.

The possible limitation of the study is the challenge of involving parents in a parallel follow-up. Even the use of routine follow-up services has been shown to be a challenge and less used especially among socially disadvantaged families [37, 38], who might benefit most from the follow up. Moreover, this web-based follow-up does not currently reach the immigrant families with no mutual language; however, these families may benefit more from clinical visits with an interpreter. However, we assume, that this web-based follow-up system will increase the involvement of the parents due to easy accessibility and availability.

In the future, this web-based system is intended to be shared with a larger number of NICUs and follow up services to increase comparison and cooperation and to enable children and parents to obtain support and help when needed. The long-term effects and the usability of the ePIPARI follow-up tool will be evaluated in this prospective study.

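### The clinic reference does not separate new from already known concerns, so sensitivity at later ages mixes detection with parents reporting what the clinic has already found

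*Protocol article*

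**What the plan says.** The aim is to find out whether ePIPARI is feasible and valid in "identifying children and families in need of further clinical interventions or support compared to clinical follow-up" (Aims). The reference is given in The evaluation of feasibility and performance: "The outcomes to be compared are: concerns requiring clinical intervention including specialist consultations, further investigations, additional controls/follow-up visits". The list continues with prescriptions, supplements and referral to treatment or therapy, and Plan for statistical analysis repeats it as the single positive category for the clinic.

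The analysis is cross-sectional at each age: "The main comparison between digital assessment and clinical evaluation for each timepoint will be done with McNemar test", with agreement and accuracy measures alongside: "sensitivity, specificity, positive and negative predictive values will be calculated (compared to clinical assessment").

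On exposure to the clinic, Participants and recruitment procedure states: "All preterm born children have the routine follow-ups regardless of their participation in the study". Blinding runs one way: "The staff of the Pediatric unit will be blinded for the data of the ePIPARI". At every age point ePIPARI asks about medications and parental concerns, and "General health/illness is evaluated by questions on any possible underlying illnesses, acute and previous infections, and different symptoms" (Health and growth).

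On intended use, the Background speaks of supplementing follow-up, cutting unnecessary routine visits, and offering digital follow-up to late preterm infants who would be called in on the strength of their answers. The Discussion wants to "reduce the number of routine visits for those who grow and develop well without compromising their safety".

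**The concern.** Several items in the positive category can last for months: extra control visits, medication, therapy. Under the definition as written, a child referred at 4 months and still under care can be clinic-positive again at 8, 12 and 24 months. The parents know of the problem and can report it. ePIPARI then agrees with the clinic, but it may have detected nothing: the information went from the clinic through the parent to the questionnaire. Staff blinding does not touch this path.

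This matters because of the intended use. Children with fewer visits, and late preterm infants with none, will have parents who lack that information. A sensitivity that pools known and new concerns does not carry over to them. The exposure is greatest at 24 months, the age used for the sample size, and in the cohort invited only for that age point, who meet ePIPARI for the first time after about two years of routine follow-up.

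**Working it through.** **1. The plan's own figure.** Inputs from Sample size and statistical power: web-based 42%, clinical 77%, correlation 0.35, power 80%, two-sided 5%.

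- Both positive: p11 = 0.42 × 0.77 + 0.35 × √(0.42 × 0.58 × 0.77 × 0.23) = 0.3234 + 0.0727 = 0.396.
- Discordant cells: 0.42 − 0.396 = 0.024 and 0.77 − 0.396 = 0.374, so pd = 0.398 and d = 0.35.
- n = [1.96 × √pd + 0.842 × √(pd − d²)]² / d² = 22.98, or 23 uncorrected. With continuity correction it is 25.8, or 26.

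The stated 26 reproduces, and the present point does not change it.

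**2. Pooled sensitivity implied by those inputs.** Taking the percentages in the order written, sensitivity against the clinic is 0.396 / 0.77 = 51.4%. Whatever the correlation, it cannot exceed 0.42 / 0.77 = 54.5%.

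**3. Splitting it.** Let f be the share of clinic positives already known. Then

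pooled = f × s_known + (1 − f) × s_new, so s_new = (pooled − f × s_known) / (1 − f).

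The documents give neither f nor the two sensitivities; all values of f and s_known below are assumptions. With pooled = 51.4%, s_new is:

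| s_known | f = 0.2 | f = 0.3 | f = 0.4 | f = 0.5 |
|---|---|---|---|---|
| 1.00 | 39.3% | 30.6% | 19.1% | 2.9% |
| 0.95 | 40.6% | 32.8% | 22.4% | 7.9% |
| 0.90 | 41.8% | 34.9% | 25.7% | 12.9% |
| 0.514 (equal) | 51.4% | 51.4% | 51.4% | 51.4% |
| 0.40 | 54.3% | 56.3% | 59.1% | 62.9% |

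Example: (0.5144 − 0.3 × 0.95) / 0.7 = 0.328. The gap between pooled and new is f × (s_known − s_new). It is zero when the two are equal, and it changes sign when known problems are flagged less often than new ones.

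If the two percentages were meant the other way round (clinic 42%), pooled sensitivity would be 0.396 / 0.42 = 94.3%. For f from 0.2 to 0.5 and s_known from 0.90 to 1.00, s_new would then lie between 88.6% and 98.6%, so the split would matter much less.

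**4. Where it can act.** Carry-over from one routine visit to the next cannot act at term, the first age point. Children born before 32 weeks or at 1500 g or less are followed to two years. Those born at 32–34 weeks have fewer visits, usually ending around one year (Information of routine follow-up as comparison). Table 3 shows no clinic visit at 18 months. The full chain to 24 months therefore concerns the very preterm group.

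**The case against.** The strongest reply has four parts.

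- **No rule says that known concerns count again.** The positive category lists actions, and a child in ongoing therapy with no new action might be coded negative. Such an abstraction rule could stand in the full protocol or analysis plan, which is not shown. This stands in part: repeat counting is inferred from an unrestricted definition. But the article does write out both clinic categories, and they contain no split.
- **The direction is not given.** A reader might infer that sensitivity is inflated and will climb with age. That requires known problems to be flagged more readily than new ones. It is plausible for the illness and medication questions. It is less clear for the motor traffic light, FinCDI-SF, PARCA-R, BITSEA and EPDS, which rate current status, and it can reverse when treatment controls a problem that the clinic still follows. This stands.
- **The use is not replacement.** A reader might take ePIPARI as meant to replace the visits. The text says supplement, and reduce for children doing well. A tool that decides who still needs a visit should also flag continuing needs, so the all-concern comparison answers a stated question and should stay. This stands.
- **Large illustrations do not fit.** Assuming 55% for new concerns, 95% for known, and 30% to 70% known gives pooled values of 67% to 83%. These exceed the 54.5% ceiling from the planning inputs as written. This stands.

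What the reply does not remove is that the pooled estimate combines two different things, and only one of them bears on reducing visits.

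**Conclusion.** The point holds as a limit on what the planned sensitivity and agreement can show after the first age points. As written, the reference pools new and known concerns in children whose parents have already heard the clinic's findings. The result may overstate or understate what ePIPARI would find with fewer or no clinic visits. Size and direction cannot be derived from the documents. With the planning inputs as written and an assumed 95% sensitivity for known concerns, a pooled 51% would correspond to 41% for new concerns at f = 0.2 and 22% at f = 0.4. It would stay at 51% if both kinds are flagged equally.

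The documents do not support saying that known concerns are counted again by rule, that inflation is established, or that every child has every visit and the term MRI: Table 3 is headed as the very preterm schedule. The sample size is unaffected. If the full plan already separates new from known concerns, the point is met.

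**What to change.** During the planned comparison with the medical records, code each clinic concern as *new at this visit* or *already known or under care from an earlier visit or the neonatal stay*. Keep the all-concern comparison as planned. Pre-specify, at each age after term that has a clinic visit, sensitivity with a 95% confidence interval separately for children with at least one new concern and children with only known concerns. Show the 24-month-only cohort apart. State in advance that any conclusion about reducing visits rests on the new-concern result.

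The cost is one extra code per concern in an abstraction that is already planned, plus a few lines of analysis text. The article says analysis is still to start, so this can be fixed beforehand.

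The real price is precision. At the stated minimum of 26, about 26 × 0.77 = 20 children are clinic-positive. If half of them have only known concerns, 10 remain. At an assumed sensitivity of 55%, the 95% half-width is about 1.96 × √(0.55 × 0.45 / 10) = 31 percentage points. A new-concern estimate at that size would be weak, and the report should say so.

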### Sample size and statistical power

Approximately 50–60 very preterm infants enter the clinical follow-up at Turku University Hospital every year and 600–650 children born prematurely are examined in the Preterm Infant Follow-up Clinic each year. Power calculations were performed to detect the children needing interventions or further follow up at 2 years of corrected age. Using data collected from ePIPARI for this age-point, we get the minimum sample size 26 participants, to achieve a power of 80% and a two-sided significance of 5% for detecting a difference of 35% between web-based and clinical evaluation (42% vs 77%) for further follow-up need. While both evaluations are made for all children, also moderate association between evaluations was assumed (correlation between paired observations was assumed to be 0.35) [Reference: Dhand, N. K., & Khatkar, M. S. (2014). Statulator: An online statistical calculator. Sample Size Calculator for Comparing Two Paired Proportions. Accessed 25 April 2023 at http://statulator.com/SampleSize/ss2PP.html]. The estimated data collection time to achieve the predetermined number of participants is 2–3 years, as not all the families agree to participate in the ePIPARI Study. The data collection is ongoing, and the analysis will start when data has been accumulated.

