**Discussion:**

The web-based tool, ePIPARI, was developed to acquire a sensitive and specific tool to detect infants and parents in need of further support and clinical interventions. This tool could allow individualized adjustments of the frequency and content of the clinical visits.

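### The sample size of 26 is powered to detect a 35-point difference, while the hypothesis is comparability, so the stated 80% is not power for the study's question

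*Protocol article*

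**What the plan says.** Four places in the Protocol article bear on this.

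- **Methods, Sample size and statistical power.** The calculation concerns the 24-month age point: "Using data collected from ePIPARI for this age-point, we get the minimum sample size 26 participants". It sets 80% power and a two-sided 5% level for "detecting a difference of 35% between web-based and clinical evaluation (42% vs 77%) for further follow-up need". The design is paired ("While both evaluations are made for all children"), and "correlation between paired observations was assumed to be 0.35". The online calculator is cited with an access date of 25 April 2023.
- **Methods, Aims.** The second hypothesis is that "it is comparable to routine clinical follow-up in recognizing children and parents in need".
- **Abstract, Discussion.** The tool "was developed to acquire a sensitive and specific tool to detect infants and parents in need of further support and clinical interventions".
- **Methods, Plan for statistical analysis.** The main comparison at each age point is a McNemar test (Bowker for more than two categories). Agreement with a 95% CI follows, then sensitivity, specificity and predictive values against the clinical assessment.

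**The concern.** A calculation that assumes a 35-point gap and asks for a good chance of detecting it answers the question of whether the two evaluations differ. The hypothesis is that they do not differ in any way that matters. If the assumed values were true, the likely outcome would be a significant test against hypothesis 2. If the test were not significant, 26 pairs would be too few to read that as comparability.

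Two further matters follow from the same section. The inputs are attributed to ePIPARI data for the same age point that the calculation covers, which raises the question of whether the same children will be tested again. And a size derived for McNemar's test says nothing about how well sensitivity and specificity will be estimated, although the stated ambition is a sensitive and specific tool.

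The risk is that a reader takes the 80% as assurance that the study can answer its validity question, or takes a non-significant test as evidence that the tool can stand beside clinical visits.

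**Working it through.** **Inputs** (all from Sample size and statistical power): p1 = 0.42, p2 = 0.77, correlation ρ = 0.35, two-sided 5%, 80% power.

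**1. The plan's own figure.** The four cells of the paired table follow from the correlation:

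- both positive: 0.42 × 0.77 + 0.35 × √(0.42 × 0.58 × 0.77 × 0.23) = 0.396
- positive only on the 42% evaluation: 0.42 − 0.396 = 0.024
- positive only on the 77% evaluation: 0.77 − 0.396 = 0.374
- both negative: 1 − 0.396 − 0.024 − 0.374 = 0.206

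Total discordance is 0.398. Then n = (1.96 + 0.842)² × 0.398 / 0.35² = 25.5, rounded up to 26. A second standard formula (Connor, with 1/d added as continuity correction) gives 25.8, also 26. Exact McNemar power at 26 pairs is 83.7%. The arithmetic is sound.

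**2. What the inputs imply about accuracy,** with the clinical assessment as reference:

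| Reading | Sensitivity | Specificity | Ceiling |
|---|---|---|---|
| Web-based 42%, clinical 77% (order written) | 0.396/0.77 = 51% | 0.206/0.23 = 90% | sensitivity ≤ 0.42/0.77 = 54.5% |
| Swapped | 0.396/0.42 = 94% | 0.206/0.58 = 36% | specificity ≤ 0.23/0.58 = 39.7% |

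Agreement is 0.396 + 0.206 = 60% and kappa is 0.27 on either reading. The ceilings do not depend on the correlation. Neither row describes a tool that is both sensitive and specific.

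**3. What a non-significant test would mean.** I used approximate McNemar power, Φ[(d√n − 1.96√pd) / √(pd − d²)], where d is the gap and pd the total discordance, with n = 26, ρ = 0.35 and 42% as the lower rate:

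- true gap of 20 points (42% against 62%): about 40%
- true gap of 10 points (42% against 52%): about 14%

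Material gaps would usually be missed. Equal rates would not settle the matter either, because McNemar's test compares marginal rates and not whether the same children are identified. With both rates at 42% and ρ = 0.35, both-positive is 0.42² + 0.35 × 0.42 × 0.58 = 0.262, so sensitivity is only 0.262/0.42 = 62%.

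**4. Precision at the stated minimum** (Clopper-Pearson 95% intervals; observed counts are illustrative):

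- 77% clinic-positive gives 0.77 × 26 ≈ 20 positives and 6 negatives. Sensitivity 18/20: 68–99%. Specificity 5/6: 36–100%.
- 42% clinic-positive gives 0.42 × 26 ≈ 11 positives and 15 negatives. Sensitivity 10/11: 59–100%. Specificity 12/15: 52–96%.
- Agreement 16/26, near the implied 60%: 41–80%.

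**5. Scale for a precision-based size.** Assume a half-width of 10 points and true values of 0.80–0.90. The number needed in the relevant group is 1.96² × s(1 − s) / 0.10², which is 62 at s = 0.80 and 35 at s = 0.90. Dividing by the share of children in that group gives the total:

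| Clinic-positive | For sensitivity | For specificity |
|---|---|---|
| 77% | 46–81 | 153–270 |
| 42% | 84–148 | 61–107 |

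**The case against.** The strongest defence is that McNemar's test is the named main comparison, that sizing a study on its main test is conventional, and that precision for additional measures is often left to a fuller document not shown here. That answers a complaint that a precision calculation is absent. It does not answer the contradiction between the direction of the power statement and the hypothesis, both of which are in the published text.

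Several stronger readings are tempting, and the article does not support them.

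- **That the analysis is circular.** A reader might infer that 42% and 77% will be tested again in the children who produced them, and might note that 11/26 and 20/26 round to those values. The article does not say how many children supplied the rates or whether they re-enter the analysis, and it describes the correlation as assumed. Re-use is a risk, not an established fact.
- **That the calculator date shows the data were complete.** It falls after the recruitment window of 4/2019–12/2022, but reaching 24 months corrected age by 25 April 2023 requires a term date no later than April 2021. Many recruits had not reached the powered age point, and data collection is described as ongoing. Planning the remainder from early data fits the text equally well.
- **That the study will stop at 26.** The article calls 26 a minimum and gives no stopping rule. An inflow of 50–60 very preterm infants a year over 45 months is about 188–225 before refusals. The section does speak of 2–3 years to reach a predetermined number, so the intended target is unclear.
- **That 26 children cannot tell a good tool from a poor one.** This goes too far for sensitivity. The intervals for 18/20 (68–99%) and 10/11 (59–100%) both exclude the 51–54.5% implied by the written order. The weak spot is specificity when only about six children are clinic-negative.

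**Conclusion.** The stated power does not serve the stated hypothesis. The 26 is correctly calculated for detecting 42% against 77%, but those values imply a sensitivity of at most 54.5% or, with the labels swapped, a specificity of at most 39.7%. So the 80% is the chance of a result that would contradict comparability. This conclusion uses only the article's own inputs and takes the clinical assessment as reference, as the analysis plan does; it holds on either labelling.

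The precision point is conditional. It applies to the stated minimum and becomes less pressing if more pairs are enrolled. The origin of the inputs is a question for the sponsor to answer, not a demonstrated fault.

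This should be fixed. It does not invalidate the study, because the data being collected can still support a sound estimate of accuracy.

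**What to change.** 1. Withdraw the 80% power statement as support for the comparability aim.
2. Justify the size by the expected 95% CI widths for sensitivity, specificity and agreement at 24 months with the pairs actually enrolled. As an illustration, with 150 pairs (an assumption) and 42% clinic-positive there are 63 positives, and 57/63 has a 95% CI of 80–96%.
3. Present the 24-month comparison as estimation, and say that a non-significant McNemar test will not be read as comparability.
4. Confirm which evaluation gave 42% and which 77%. The word order suggests web-based first, and the implied weakness moves from sensitivity to specificity if it is the other way round.
5. State how many children supplied those rates. If the McNemar test is kept as confirmatory, either state that these children are separate from the analysis set or exclude them.

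The cost is mainly rewording, with no extra recruitment. The stated justification becomes less favourable. If children are excluded, the confirmatory set shrinks by a number that cannot be given from the article.
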